## Abstract

Physiological training responses depend on sympathetic (SNS) and parasympathetic nervous system (PNS) balance. This activity can be measured using heart rate variability (HRV). Such a measurement method can favor individualized training planning to improve athletes’ performance. Recently, HRV-guided training has been implemented both on professional and amateur sportsmen and sportswomen with varied results. There is a dearth of studies involving professional endurance athletes following a defined HRV-guided training protocol. The objectives of the proposed protocol are: (i) to determine changes in the performance of high-level athletes after following an HRV-guided or a traditional training period and (ii) to determine differences in the athletes’ performance after following both training protocols. This will be a 12-week cluster-randomized controlled protocol in which professional athletes will be assigned to an HRV-based training group (HRV-G) or a traditional-based training group (TRAD-G). TRAD-G will train according to a predefined training program. HRV-G training will depend on the athletes’ daily HRV. The maximal oxygen uptake (VO_2max_) attained in an incremental treadmill test will be considered as the primary outcome. It is expected that this HRV-guided training protocol will improve functional performance in the high-level athletes, achieving better results than a traditional training method, and thus providing a good strategy for coaches of high-level athletes.

## 1. Introduction

It is known that training is essential for improving physical performance [1] and that optimizing training for performance improvement in athletes is an important area of research within exercise physiology and sports medicine [2,3,4]. In this regard, different training methods for performance improvement have been tried and tested, such as intensified training [2,5,6] and submaximal tests [7]. However, it is also recognized that using the same standardized training program for a group of athletes can provoke a wide range of reactions in terms of performance and physiological adaptations [8,9].

As stated by Schmitt, Willis, Fardel, Coulmy, and Millet [10], an important component of the interindividual variability in physiological responses to standardized training is related to the balance between the parasympathetic (PNS) and sympathetic (SNS) activity of the autonomic nervous system (ANS) [11,12]. Heart rate variability (HRV) is one of the indicators that allows the noninvasive study of autonomic nervous system activity in its sympathetic and parasympathetic branches [13,14]. HRV is understood as the variation in the time interval between two consecutive heartbeats. It is obtained by calculating the time interval that elapses between two consecutive R waves (i.e., RR interval fluctuation) on an electrocardiogram (ECG) [15]. The period between beats is not constant; consequently, high HRV values are associated with an efficient ANS, which promotes behavioral adaptation and cognitive flexibility during stress [16], whilst low HRV values are indicative of an inefficient ANS, resulting in maladaptive responses to stress and perceived threats [15]. Furthermore, HRV is considered to be an indicator of cardiovascular health level [17].

Given that the SNS is responsible for changes in heart rate (HR) due to stress, and that the HR is one of the first parameters used to control the body’s functional capacity [18], HRV analysis has been established as a useful method for assessing the heart’s ability to adapt to both endogenous and exogenous loads [19], and can be used for the individual assessment of responses to training loads. Indeed, in recent years, HRV has been used to analyze these imbalances between SNS and PNS in athletes [20] and to evaluate different aspects related to training [21] such as exercise intensity and duration [22], recovery and overtraining [23], training load [24] or psychophysiological profiles [25].

The control of training based on HRV, as an indicator of the precompetitive physical and psychological state in athletes, enables coaches and scientists to use these HRV records to adapt the recovery and training loads to each athlete in search of a better sports result. As indicated by Ortigosa-Márquez, Reigal, Carranque, and Hernández-Mendo [26], high HRV values indicate more parasympathetic than sympathetic activation in an athlete and, therefore, better recovery and preparation for dealing with high-intensity training sessions.

Traditionally, HRV has been measured with ECG [14]. One of the ways of quantifying HRV is through rMSSD (the root mean square of successive differences between adjacent RR intervals) [26] since it is a temporal statistical parameter that reports those variations occurring over the short term between RR intervals [27] and it is used to observe the influence of the SNP on the cardiovascular system [18]. Currently, there are other validated tools for determining HRV that facilitate measurement, such as the Kubios HRV, Elite HRV, Mobile Lab and HRV4Training applications (apps).

In recent years, experimental studies have been carried out evaluating HRV-guided training in endurance athletes. These studies have been conducted both on elite athletes in sports such as cycling [24] and skiing [10], and with amateur endurance athletes [28,29,30,31]. One should take into account the scarcity of studies that have been published to date, especially on elite-level endurance athletes, as well as the absence of a common protocol to follow in this type of research.

The protocol proposed in the present study contributes to the scientific literature in this field in several ways: (i) it proposes research focused on elite athletes, a sample population for which only two experimental studies have been carried out to date; (ii) the protocol is intended to research endurance runners, for which we are not aware of any research having been carried out on this type of sample and with these characteristics at the international level. Therefore, it is a novel study aiming to provide empirical support for HRV-guided training in long-distance runners, adapting daily training to the physiological responses of each individual athlete. The performance of these athletes could be compared to that of another group of long-distance runners who carry out traditional training over the same period of time.

Until just a few years ago, conducting research of this type, involving daily HRV measurements on each athlete and then adapting training based on these data, was only possible with the collaboration of high-cost laboratories. This study tests the use of noninvasive, commercial, low-cost and publicly accessible technology to evaluate the physiological responses obtained by adapting training to HRV.

Based on everything described above, we hypothesize that HRV-guided training will: (i) improve functional performance in high-level athletes and (ii) produce better performance results than a traditional training method. The objectives of the proposed protocol are: (i) to determine changes in the performance of high-level athletes after following an HRV-guided or a traditional training period, and (ii) to determine differences in the athletes’ performance after following both training protocols.

This will be a 12-week cluster-randomized controlled trial protocol in which professional athletes are assigned to either an HRV-based training group (HRV-G) or a traditional-based training group (TRAD-G). A block randomization method will be chosen to randomly assign participants to interventions in equally sized sample groups. This protocol has been designed following the Standard Protocol Items: Recommendations for Interventional Trials (SPIRIT) Statement [32]. To describe the intervention, the TIDieR (Template for Intervention Description and Replication) checklist by Hoffmann et al. [33] has been used.

## 2. Materials and Methods

### 2.1. Study Setting

To detect an intervention-related effect in professional athletes, other studies with similar protocols [24,31] compared athletes from two clubs or associations. Similarly, our sample will comprise athletes from two sport institutions in Almería (Spain): the C.D. Atletas de Almería, based in the city of Almería (Spain) and the Asociación Espeleológica Velezana, based in Vélez Rubio (Spain).

### 2.2. Eligibility Criteria

The inclusion criteria for participating in the program will be: (i) to belong to the Spanish Athletics Federation; (ii) to have been training and competing in Spanish Athletics Federation competitions for at least two years; and iii) to be in the first third of the classification for the last five races of the previous season. Regarding the exclusion criteria, the following will be taken into account: (i) having cardiovascular pathologies, abnormal blood pressure parameters or diagnosed respiratory problems; (ii) being treated for psychological problems, or regularly taking a drug(s) that has a direct or indirect effect on the nervous system (e.g., anxiolytics, antidepressants or neuroleptics); (iii) substance use that is not permitted by the International Association of Athletics Federations (IAAF); (iv) occasional consumption of medication for a disease related to the cardiorespiratory system (e.g., influenza) that might alter performance and (v) not performing at least 90% of the workouts during the intervention.

The trial steering members will be responsible for checking that the subjects interviewed meet the inclusion criteria. The Spanish Athletics Federation’s medical team will certify that the subjects do not meet any of the exclusion criteria. After being informed of the study design and potential risks, all athletes will sign a written informed consent document. The model consent form is shown in Appendix A.

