### 2.3. Interventions

Based on the methodology used by Javaloyes et al. [24] and Vesterinen et al. [31], the intervention will be divided into two training periods for both study groups (HRV-G and TRAD-G): a four-week preparation period (PR) and an eight-week training period (TR). Both will maintain the weekly training volume. The training carried out will mainly be running. The PR period will be common to both groups and will be a familiarization phase for the training sessions and their intensities. During this period, the training intensity will gradually increase for the first three weeks and then decrease in the fourth week. This will mean three weeks of overloading and one week of recovery (3:1). The training to be carried out by the athletes is presented in more detail in Table 1. In the TR period, each group will carry out the corresponding intervention. The TRAD-G group will train according to a predefined training program, which will include sessions carried out at low intensity (approximately 50% of the total), and other sessions of moderate and high intensity, with a structure similar to that carried out during the PR period (Table 2). The training prescribed to the HRV-G group will depend on the subjects’ HRV, in accordance with authors such as Javaloyes et al. [24], Kiviniemi, Hautala, Kinnunen, and Tulppo [34], and Lamberts, Swart, Noakes, and Lambert [35].

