To quantify the HRV, a Smartphone application known as “HRV4Training” (see http://www.hrv4training.com/) will be used. This tool has been validated by Plews et al. [36], showing a low typical estimate error (CV% (90% CI) = 3.8 (3.1; 5.0)) and a clear electrocardiographical correlation (r = 1.00 (1.00; 1.00)). It provides the root mean sum of the successive differences between R – R intervals (rMSSD) data using photoplethysmography. rMSSD is more suitable and reliable than other indexes [13,37]; nonetheless, the HRV data will be transformed by taking the natural logarithm, thus allowing parametric statistical comparisons that assume a normal distribution. In this way, a 7-day rolling average will be calculated (LnrMSSD_7-d_). The PR period will be used as a standardized phase to obtain the baseline LnrMSSD_7-d_ and its range of normality (upper and lower limits). Following the indications of Plews, Laursen, Kilding, and Buchheit [38], this will be calculated as the mean ± 0.5 × SD. During the TR period, the LnrMSSD_7-d_ will be calculated daily in order to adapt the training prescribed to the HRV-G athletes. Moreover, the range of normality will be updated weekly. If the LnrMSSD_7-d_ is within the range of normality, the athletes will perform a moderate or high-intensity session. If the weekly LnrMSSD_7-d_ average falls below the normal range, a low intensity workout or rest will be undertaken. Athletes will perform a maximum of two consecutive sessions of moderate or high intensity; likewise, they will not accumulate more than two consecutive rest sessions. The modified scheme of Kiviniemi et al. [34] presented in Figure 1 will be followed.

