### 2.6. Recruitment

Each club or association involved in athletics in Almería (Spain) will be screened to identify the percentage of high-level or professionally federated athletes. When there are at least 7 high-level or professionally federated athletes, the club/association officers will be contacted by telephone to inform them of the study objective. Once they agree, an informative talk will be carried out with the athletes and the coach to inform them of the study objective, the time period in which it will take place, and the required commitment by the athletes to measure their daily HRV according to the established protocol, to attend the pre and post-test sessions and to attend at least 90% of the training sessions. The coaches will be informed of the required commitment to adapt each athlete’s training session to the daily HRV score if their club is randomized into the HRV-G group. If they agree to participate, then they will have to sign the written consent and meet the eligibility criteria necessary to be recruited into the study. The recruitment process will be conducted by the trial steering members.

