### 2.8. Data Analysis

Data will be analyzed using Jamovi (Jamovi Project 2018, version 0.9.1.7, Sydney, Australia) and RStudio 3.15.0 software (PBC, Boston, MA, USA). Prior to data analysis, the Shapiro Wilk test and the Levene test will be performed to determine the normal distribution of the variables and the homogeneity of variance. Descriptive data will be reported as mean ± SD and range. All the data will be analyzed based on the intention-to-treat principle (last observation carried forward). If the sample is normally distributed, Student’s t-test will be calculated to compare variables before and after the intervention. For a variable to be considered as having a normal distribution, 95% of values will have to be within two standard deviations of the mean. If the sample is nonparametric, the U-Mann Whitney test will be used to compare variables before and after the intervention. The standardized mean differences (Cohen’s effect size) will be calculated together with the 95% confidence intervals [49]. The effect sizes (ES) will be calculated using Cohen’s d [49]. The relationship between variables will be assessed using the Pearson r correlation coefficient. If r is higher than 0.7, the determination coefficient (r^2^) will be used to determine the percentage of Y variation with regard to the X variation. Significance will be accepted at *p* ≤ 0.05.

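### The 90% workout rule is listed as an exclusion criterion but can only be known after allocation; it conflicts with the intention-to-treat statement, and the protocol does not say which governs

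*Protocol article*

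**What the plan says.** Section 2.2 (Eligibility Criteria) gives five exclusion criteria. The first four concern health, medication and prohibited substances. The fifth is "not performing at least 90% of the workouts during the intervention". The same section says that the federation's "medical team will certify that the subjects do not meet any of the exclusion criteria".

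Section 2.3 (Interventions) fixes what the intervention covers: "the intervention will be divided into two training periods for both study groups (HRV-G and TRAD-G"), namely four weeks of preparation (PR) and eight weeks of training (TR). The arms differ in TR. "The TRAD-G group will train according to a predefined training program", whereas "The training prescribed to the HRV-G group will depend on the subjects’ HRV"; when the rolling HRV average is below range, "a low intensity workout or rest will be undertaken".

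Section 2.6 (Recruitment) uses the same 90% differently, as something athletes undertake at enrolment: "to attend at least 90% of the training sessions".

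Section 2.8 (Data Analysis) states: "All the data will be analyzed based on the intention-to-treat principle (last observation carried forward"). No per-protocol set is named.

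**The concern.** An exclusion criterion that depends on behaviour during the intervention cannot work as an entry check. If it is enforced, athletes leave the comparison after allocation because of something the assigned programme may itself have influenced. An analysis that keeps all athletes as assigned does not allow that.

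The arms also do not share a common notion of a workout. TRAD-G has a predefined list of sessions. In HRV-G the sessions follow the athlete's HRV and may be rest. A missed session in one arm need not mean the same as a missed session in the other, so the rule could select different kinds of athlete in each arm. The athletes most likely to fall below 90% are plausibly those who were tired, ill or injured, and that may be related to the change in VO2max.

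At stake are who enters the primary comparison and, with arms of 7, how many remain.

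**Working it through.** **1. The rules side by side.** Take an athlete who performs 85% of the workouts.
- Section 2.2 makes the athlete excluded.
- Section 2.6 says only that a commitment was not kept.
- Section 2.8 says the athlete's data are analysed.

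No section ranks these. The medical certification in Section 2.2 cannot cover the fifth criterion, which is unknown at entry. The text does not date the allocation (Figure 2 is not shown), but the TR workouts follow it on any reading, since the arms separate there. Section 2.6 speaks of clubs being randomised; the point is unchanged, because the exclusion would act athlete by athlete afterwards.

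Last observation carried forward does not settle it. Section 2.4 has one pretest (week 5) and one post-test (week 12), so a missing post-test is replaced by the pretest value, a change of zero. The same athlete could be left out, scored as zero change, or analysed on a measured week-12 value.

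**2. How many missed sessions breach 90%.** Counts from Tables 1 and 2:

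| Period | High/moderate | Low | Total |
|---|---|---|---|
| PR, weeks 1-4 | 1+2+3+0 = 6 | 10-14 | 16-20 |
| TR, weeks 5-12 | 1+2+3+0+1+1+3+0 = 11 | 20-28 | 31-39 |
| PR + TR | 17 | 30-42 | 47-59 |

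The largest permitted number of misses is the whole-number part of 0.10 × N.
- PR + TR, N = 47: 4 permitted; the fifth gives 42/47 = 89.4%.
- PR + TR, N = 59: 5 permitted; the sixth gives 53/59 = 89.8%.
- TR only, N = 31 or 39: 3 permitted; the fourth gives 27/31 = 87.1% or 35/39 = 89.7%.

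No such count is possible for HRV-G, whose sessions depend on HRV.

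**3. How easily this is reached (assumption: independent misses at rate p).** P(breach) = 1 − BinomCDF(permitted misses; N, p).
- PR + TR, over N = 47 to 59: 4-10% at p = 0.05; 38-55% at p = 0.10.
- TR only, over N = 31 to 39: 7-13% at p = 0.05; 38-56% at p = 0.10.

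The document gives no miss rate, so these values only show sensitivity.

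**4. Effect on numbers and power.** The stated 93% in Section 2.5 is reproduced by a two-group F-test with a between/within variance ratio of 2. The noncentrality is 7 × 2 = 14 on 1 and 12 degrees of freedom, α = 0.05, and the power is 0.929. This is a standardised difference of √(2 × 2) = 2. On the same basis power is 0.904 for 6 v 7, 0.876 for 6 v 6 and 0.791 for 5 v 5. Each exclusion removes 1/7 = 14% of a planned arm.

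**5. Possible bias (illustration only).** Assume no true effect, the planning SD of 1.5 mL/kg/min, a correlation ρ of 0.3 to 0.5 between adherence and outcome, and removal of the least adherent fraction q. The mean of an arm then rises by ρ × 1.5 × φ(z_q)/(1 − q).
- 1/7 removed from one arm only: 0.12 to 0.20.
- 2/7 from one arm only: 0.21 to 0.36.
- 2/7 v 1/7: 0.10 to 0.16.
- Equal removal: 0.

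The shift favours whichever arm loses more athletes. The document does not say which arm that would be.

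**The case against.** The best defence is that Section 2.8 is the only place that defines who is analysed, and it says everyone. Section 2.6 treats 90% as a commitment, and the certification in Section 2.2 reads as an entry check. On this view one clause is misplaced and the analysis is sound.

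Much of that stands. A reader might infer that athletes below 90% are in fact deleted from the analysis. The article does not say so; this is only the natural meaning of an exclusion criterion, and Section 2.8 contradicts it. What does not stand is that the matter is settled, because nothing gives Section 2.8 precedence over Section 2.2.

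A reader might also infer that HRV-G rest days count as performed, so that the rule is more lenient in that arm. No section says how rest enters the count. It could count as performed or drop out of the denominator, and Section 2.3 also limits consecutive rest sessions. The different prescriptions are explicit; an advantage for either arm is not.

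Nor do the documents show that the fourth missed session excludes an athlete. That holds only if the TR weeks alone are counted, and Section 2.3 defines the intervention as PR plus TR.

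Finally, 7 is the screening minimum for a club in Section 2.6, so more athletes might be available, and the loss of power from one or two exclusions is modest on the plan's own basis. This is fair, but it bears on numbers and not on selection.

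**Conclusion.** The contradiction holds on the printed text alone: a criterion observable only after allocation stands as an exclusion beside an intention-to-treat analysis of all data, and neither is given precedence. The population for the primary comparison is therefore undetermined for any athlete below 90%.

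If the criterion is enforced, the comparison of HRV-G with TRAD-G could be biased. The documents do not support saying that it will be, or in which direction: the bias depends on unequal exclusion between arms and on a link between adherence and outcome, neither of which can be derived from them. What can be fixed is the threshold for TRAD-G (fifth or sixth missed session over 12 weeks, on the counts in Tables 1 and 2) and the cost per exclusion (14% of a planned arm of 7). The breach probabilities and the shifts in mL/kg/min rest on assumed miss rates and correlations and should not be quoted as estimates.

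**What to change.** - Delete the fifth item from the exclusion criteria in Section 2.2. The 90% commitment in Section 2.6 can stay as an adherence target.
- State in Section 2.8 that every randomised athlete is analysed in the assigned group, whatever the adherence.
- Seek the already scheduled week-12 tests from athletes who reduce or stop training, so that fewer values have to be carried forward.
- Use at least 90% adherence only to define a labelled secondary per-protocol sensitivity set. Say whether PR counts and how a prescribed rest day is handled, so that workouts are counted comparably in both arms.

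The cost is protocol wording, a few post-tests on low-adherence athletes, and possibly a somewhat diluted effect estimate. No training rule changes.
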